|  |                                                                                                                                                                                  |                                                                                                                                                                                                                                                                                                                                     |
|--|----------------------------------------------------------------------------------------------------------------------------------------------------------------------------------|-------------------------------------------------------------------------------------------------------------------------------------------------------------------------------------------------------------------------------------------------------------------------------------------------------------------------------------|
|  | 
Exploratory efficacy against infection
 
 
To assess efficacy of the candidate ChAdOx1 nCoV-19 against SARS-CoV-2 infection
 
 | 
a) PCR* positive SARS-CoV-2 infection
 
b) Differences in viral loads between those with severe, mild, and asymptomatic PCR+* SARS-CoV-2 infections
                                                                                                                                                                     |
|  | 
Compare safety, reactogenicity and immunogenicity between different manufacturing batches of ChAdOx1 nCoV-19 used in COV001 and COV002
                                    | 
a) Differences in safety, reactogenicity and immunogenicity profiles between Group 1 in COV001 and Group 5 in COV002 (proportion of Grade 3 solicited AEs, occurrence of fevers, seroconversion rates at D28, neutralising antibody titres and differences in T-cell responses at D14).
                                      |

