| Primary    | To assess efficacy of the candidate ChAdOx1 nCoV-19 against COVID-19 in adults aged 18 years and older. | Virologically confirmed (PCR* positive) symptomatic cases of COVID-19                                                                                                                                                                                                                                                                                                                                                                                   | Throughout the study                                                                                                                                                                                                                                                            |
| Co-Primary | To assess the safety of the candidate vaccine ChAdOx1 nCoV-19 in adults                                 | Occurrence of serious adverse events (SAEs) throughout the study duration.                                                                                                                                                                                                                                                                                                                                                                              | Throughout the study                                                                                                                                                                                                                                                            |

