|  |                                                                                                                                                                                  |                                                                                                                                                                                                                                                                       |                                                                                                                                            |
|--|----------------------------------------------------------------------------------------------------------------------------------------------------------------------------------|-----------------------------------------------------------------------------------------------------------------------------------------------------------------------------------------------------------------------------------------------------------------------|--------------------------------------------------------------------------------------------------------------------------------------------|
|  | 
Exploratory efficacy against infection
 
 
To assess efficacy of the candidate ChAdOx1 nCoV-19 against SARS-CoV-2 infection
 
 | 
a) PCR* positive SARS-CoV-2 asymptomatic infection
 
b) Differences in viral loads between those with severe, mild, and asymptomatic PCR+* SARS-CoV-2 infections.
                                                                                         | Throughout the study                                                                                                                       |
|  | Measure exposure to COVID-19                                                                                                                                                     | Reported by weekly survey to collect information about cases amongst household contacts and friends, contact with the general public, infection control procedures                                                                                                    | Weekly throughout the study                                                                                                                |

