After review of all available data from animal studies and at least 4 weeks safety and immunogenicity data from the first 54 participants receiving ChAdOx1 nCoV-19 in COV001, following DSMB review, enrolment into Groups 1, 4, 5 & 6 will commence. A minimum of 7 days safety data from group 1 will be reviewed by the DSMB prior to enrolment of participants into group 2. Participants will be randomised to ChAdOx1 nCoV-19/MenACWY on a 3:1:3:1 ratio in groups 1 and 7, and 5:1:5:1 ratio in groups 2 and 8, 1:1 in groups 4, 5a, 5b, 5c, 6, 9 and 10, and 5:1 in group 5d. Groups 5e and 5f will be open label and therefore, volunteers will not be randomised. Participants in groups 4, 6, 9 and 10 will be advised to take prophylactic paracetamol for 24 hours (1000 mg every 4-6 hours) from the time of vaccination to reduce the likelihood of fever. The sequence of enrolment of participants over the age of 56 years is outlined in section 7.3.2.2. Up to 100 volunteers in group 4 will be invited to receive a booster dose of  $2.2 \times 10^{10}$  vp (qPCR) 4-6 weeks after prime. All remaining volunteers in group 4 and all participants in group 6 will be invited to receive a booster dose of 0.5mL ( $3.5 - 6.5 \times 10^{10}$  vp, Abs 260, corrected for PS80) at least 4 weeks after prime. Participants who were originally randomised to receive a single dose in groups 1 (a1 and a2), 2 (a1 and a2) and 5 (a1 and a2) will be invited to receive a booster dose of 0.5mL ( $3.5 - 6.5 \times 10^{10}$  vp, Abs 260, corrected for PS80) at the earliest available opportunity, with a minimum 4 weeks interval from prime.

Safety will be assessed in real time. The DSMB will periodically assess safety and efficacy data every 4-8 weeks and/or as required.

Participants will be followed over the duration of the study to record adverse events and episodes of virologically confirmed symptomatic COVID-19 cases. Participants will be tested for COVID-19 if they present with a new onset of fever ( $\geq 37.8$  C) OR cough OR shortness of breath OR anosmia/ageusia.

Weekly testing for PCR+ infection with SARS-CoV-2 using home test kits will also be undertaken in partnership with the Department of Health and Social care national community testing programme, subject to testing resource availability.

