## **9.6 Interim and primary analyses of the primary outcome**

It is planned that the primary evidence of efficacy and safety for the ChAdOx1 nCoV-19 vaccine will be based on global analyses utilizing studies COV001 (the UK P1/2 study), COV002 (the UK P2/3 study), COV003 (the Brazil P3 study) and COV005 (the South Africa P1/2 study) including a pooled analysis across the studies. As such the interim and primary analyses for the primary outcome will be based on cases accumulated across multiple studies, details of which will be specified within the MAA SAP rather than for each individual study. Interim and primary data cuts from this study will therefore be carried out to support the pooled analysis.

The global MAA SAP allows for interim and primary analyses to be conducted once sufficient eligible cases have accumulated, where the overall type 1 error is controlled at the 5% level using a flexible alpha-spending approach that accounts for the incorporation of data from this study into pooled interim analyses under the global MAA SAP.

Evidence of efficacy will be determined if the lower bound of the multiplicity adjusted confidence interval is greater than a 20% threshold. The primary analysis will have approximately 90% power assuming a vaccine efficacy of 60%. A flexible alpha spending approach will be implemented to allow an earlier primary analysis in the situation where accumulation of eligible cases were lower than expected.

Evidence of efficacy at an interim or primary analysis of pooled data will not be considered a reason to stop the trial, but instead will be interpreted as early evidence of efficacy. However if an interim analysis

demonstrates evidence of efficacy then a study level analysis according to the study SAP may be used to support study level evidence of efficacy.

Participants who received other vaccines during the trial will have their vaccination data recorded. If a participant receives an approved or licensed COVID-19 vaccine outside of the trial procedures (such as through their workplace) this information will be recorded. Participants will be censored in the analysis at the time of their vaccination with the alternative COVID-19 vaccine.

If a large proportion of trial volunteers are vaccinated in this way then an exploratory, non-randomised analysis of efficacy according to vaccine(s) received will be undertaken if data are sufficient.

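### Synopsis and Section 4 give different outcomes for efficacy against infection, and Section 4's asymptomatic-only version does not estimate that efficacy

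*Protocol*

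**What the plan says.** The objective reads the same in the Synopsis (tertiary objectives) and in Section 4 (Objectives and Endpoints): "To assess efficacy of the candidate ChAdOx1 nCoV-19 against SARS-CoV-2 infection". Outcome a) differs. The Synopsis has "PCR* positive SARS-CoV-2 infection"; Section 4 has "PCR* positive SARS-CoV-2 asymptomatic infection". Outcome b) is common to both and covers the whole range of infection: "Differences in viral loads between those with severe, mild, and asymptomatic PCR+* SARS-CoV-2 infections".

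The symptomatic part of infection is the primary endpoint: "Virologically confirmed (PCR* positive) symptomatic cases of COVID-19". Infections without symptoms would be found mainly by home swabs; Section 5 says "Weekly testing for PCR+ infection with SARS-CoV-2 using home test kits will also be undertaken", subject to testing resources. The Statistics chapter defines the symptomatic endpoint in Section 10.1.1 and says nothing about which infection outcome applies.

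**The concern.** The added word in Section 4 changes the quantity being estimated. A count of asymptomatic infections answers a different question from a count of infections. It excludes everyone who was infected and had symptoms, and its size in the vaccine arm depends on two opposing effects: infections prevented, which lower it, and symptomatic infections made asymptomatic, which raise it. A vaccine that reduces infection could therefore appear to do little against infection, or to increase it.

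Two analysts could each follow the protocol faithfully and report different results under the same objective. An SAP cannot agree with both cells, so the conflict has to be settled in the protocol.

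**Working it through.** **Text comparison.** The two rows share the objective and outcome b). They differ only in whether outcome a) is restricted to asymptomatic infection. Neither is amendment-log text. No row in Section 4 counts symptomatic and asymptomatic NAAT-positive infections together.

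**Size of the difference.** The protocol gives no figure to reproduce here, so this is an illustration on stated assumptions. Let VE_inf be efficacy against any infection, s_c the symptomatic share of control infections and s_v the symptomatic share of vaccinee infections. With equal follow-up and complete detection,

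VE_asym = 1 - (1 - VE_inf)(1 - s_v)/(1 - s_c)

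VE_sym = 1 - (1 - VE_inf) s_v/s_c

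Assume s_c = 0.5.

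| VE_inf | s_v | VE_asym | VE_sym |
|---|---|---|---|
| 50% | 0.30 | 1 - 0.5 × 0.70/0.5 = 30% | 1 - 0.5 × 0.30/0.5 = 70% |
| 40% | 0.25 | 1 - 0.6 × 0.75/0.5 = 10% | 1 - 0.6 × 0.25/0.5 = 70% |
| 30% | 0.20 | 1 - 0.7 × 0.80/0.5 = -12% | 1 - 0.7 × 0.20/0.5 = 72% |
| any | 0.50 | equal to VE_inf | equal to VE_inf |

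The last row is the no-shift case: if vaccination leaves the symptomatic share unchanged, the two outcomes give the same efficacy.

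**Check at the protocol's planning value.** The first three rows imply symptomatic VE of 70% to 72%, above the 60% assumed in Section 9.6. Holding VE_sym at 60% with s_c = 0.5, VE_inf = 0.5 × 0.60 + 0.5 × VE_asym, so VE_asym = 2 × VE_inf - 0.60. Infection VE of 40%, 30% and 20% then reads as asymptomatic VE of 20%, 0% and -20%. At infection VE of 60% the two agree.

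**Check by counting cases.** Take 100 control infections, 60 symptomatic and 40 not, with VE_sym at 60%. The vaccine arm has 24 symptomatic cases. Suppose infections that would have been asymptomatic anyway fall by 60% (40 to 16), and half of the 36 averted symptomatic cases still occur as asymptomatic infections (18). Asymptomatic cases number 34, so VE_asym = 1 - 34/40 = 15%, while VE_inf = 1 - (24 + 34)/100 = 42%. With no conversion, both are 60%.

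**The case against.** The strongest reply is that little depends on this. The outcome is tertiary and carries no alpha, power or success criterion; the 20% threshold, 90% power and type 1 error control in Sections 9.6 and 9.7 belong to the primary outcome. That stands.

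A reader might go further and infer that Section 4 leaves the trial unable to assess efficacy against infection. The documents do not support that. Section 9.2 (Primary efficacy) has all PCR-positive results assessed, including weekly home swabs and qualifying outside tests, so any infection can be derived. Seroconversion to non-Spike antigens is also a secondary outcome, although under another objective. What is missing is a named outcome for the combination. Adding primary cases to asymptomatic cases may not supply it, because someone positive with only symptoms outside the primary list could fall in neither category.

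A reader might also infer that this outcome is the trial's evidence on transmission, or the reason for weekly swabbing. The protocol says neither, and Section 9.2 also feeds weekly positives into primary-outcome assessment.

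The illustration depends on the vaccine lowering the symptomatic share, and the shares used are not in the documents. That is why the no-shift case is shown.

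Finally, the pooled outcome has a weakness of its own. Sections 5 and 7.3.5 make weekly swabbing depend on resources, while symptomatic participants are tested separately. Where swabbing is incomplete to the same degree in both arms, the pooled count over-represents symptomatic infections and its VE moves from VE_inf towards VE_sym: in the first row of the table, from 50% with complete swabbing towards 70% with none. This calls for a caveat and for reporting both outcomes. It does not make the asymptomatic-only count a measure of infection.

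**Conclusion.** The inconsistency is real and unresolved within the protocol, and Section 4's outcome does not match its own objective. Under the stated assumptions the asymptomatic measure understates infection VE by 20 to 42 percentage points (50 against 30, 40 against 10, 30 against -12); with no change in the symptomatic share the gap is zero. The direction and size rest on the assumed 50% symptomatic share in controls and on the assumed falls in vaccinees.

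The consequence is limited to one exploratory result. The primary efficacy conclusion does not change, and no data are lost. Asymptomatic infection remains a legitimate outcome in its own right; the fault is in using it alone under an objective about infection. The SAP was not available for this review and may define both outcomes, but it would still have to depart from one of the two protocol cells.

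**What to change.** In Section 4, make any NAAT-positive infection regardless of symptoms the outcome for this objective, matching the Synopsis. List asymptomatic NAAT-positive infection as a separate outcome, in the Synopsis as well, and report both.

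Section 7.6.1 places the completed primary analysis before the unblinding of all participants, so the change should carry a date and a justification. The report should state that weekly swabbing was resource-limited and that the pooled count may over-represent symptomatic infections where swabbing was incomplete.

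The cost is a small edit to the two tables, a matching SAP line and a short reporting caveat. No new data are needed.

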## 5 TRIAL DESIGN

This is a Phase 2/3, participant-blinded individually randomised controlled trial in adults in the UK, administering either a single dose or two-doses of ChAdOx1 nCoV-19 or licensed MenACWY vaccine via IM injection. Additional steps may be taken to keep clinical investigators assessing the primary efficacy endpoint blinded to group allocation, where this is possible and practical to do so. All data from participants with PCR (or other nucleic acid amplification test) -positive swabs will be assessed for inclusion in the primary efficacy analysis by two blinded assessors who will independently review each case according to pre-specified criteria as detailed in the statistical analysis plan, to classify each for inclusion in the primary and secondary outcomes. *Protocol V19.0*: Exploratory COVID-19 disease endpoints may be assessed by trained study site staff following pre-specified criteria, rather than independent blinded assessors.

After review of all available data from animal studies and at least 4 weeks safety and immunogenicity data from the first 54 participants receiving ChAdOx1 nCoV-19 in COV001, following DSMB review, enrolment into Groups 1, 4, 5 & 6 will commence. A minimum of 7 days safety data from group 1 will be reviewed by the DSMB prior to enrolment of participants into group 2. Participants will be randomised to ChAdOx1 nCoV-19/MenACWY on a 3:1:3:1 ratio in groups 1 and 7, and 5:1:5:1 ratio in groups 2 and 8, 1:1 in groups 4, 5a, 5b, 5c, 6, 9 and 10, and 5:1 in group 5d. Groups 5e and 5f will be open label and therefore, volunteers will not be randomised. Participants in groups 4, 6, 9 and 10 will be advised to take prophylactic paracetamol for 24 hours (1000 mg every 4-6 hours) from the time of vaccination to reduce the likelihood of fever. The sequence of enrolment of participants over the age of 56 years is outlined in section 7.3.2.2. Up to 100 volunteers in group 4 will be invited to receive a booster dose of  $2.2 \times 10^{10}$  vp (qPCR) 4-6 weeks after prime. All remaining volunteers in group 4 and all participants in group 6 will be invited to receive a booster dose of 0.5mL ( $3.5 - 6.5 \times 10^{10}$  vp, Abs 260, corrected for PS80) at least 4 weeks after prime. Participants who were originally randomised to receive a single dose in groups 1 (a1 and a2), 2 (a1 and a2) and 5 (a1 and a2) will be invited to receive a booster dose of 0.5mL ( $3.5 - 6.5 \times 10^{10}$  vp, Abs 260, corrected for PS80) at the earliest available opportunity, with a minimum 4 weeks interval from prime.

Safety will be assessed in real time. The DSMB will periodically assess safety and efficacy data every 4-8 weeks and/or as required.

Participants will be followed over the duration of the study to record adverse events and episodes of virologically confirmed symptomatic COVID-19 cases. Participants will be tested for COVID-19 if they present with a new onset of fever ( $\geq 37.8$  C) OR cough OR shortness of breath OR anosmia/ageusia.

Weekly testing for PCR+ infection with SARS-CoV-2 using home test kits will also be undertaken in partnership with the Department of Health and Social care national community testing programme, subject to testing resource availability.

Moderate and Severe COVID-19 disease will be defined using clinical criteria. Detailed clinical parameters will be collected from medical records and aligned with agreed definitions as they emerge. These are likely to include, but are not limited to, oxygen saturation, need for oxygen therapy, respiratory rate and other vital signs, need for ventilatory support, Xray and CT scan imaging and blood test results, amongst other clinically relevant parameters.

Accumulated safety data from COV001 will be reviewed before commencing enrolment.

To account for the multisite recruitment activity, it is recognised that the number of volunteers enrolled into each group 9 and 10 will be 1000 +/-10%.

#### HIV -Group 12: open-label

This is a single arm group whereby up to 60 HIV infected individuals who are stable on antiretroviral therapy (ARV) will be recruited and receive ChAdOx1 nCoV-19 vaccination according to the schedule of attendance described in table 14.

## 5.1 Study groups

| Group                    | Vaccine                                                                                                                                                                                 | Number of Volunteers                         | Age group of volunteers   |
|--------------------------|-----------------------------------------------------------------------------------------------------------------------------------------------------------------------------------------|----------------------------------------------|---------------------------|
| Randomised groups |                                                                                                                                                                                         |                                              |                           |
| Group 1 ****             | a1) Single dose ChAdOx1 nCoV19 vaccine, 5x10  vp (Abs 260)*, OR
a2) Single dose MenACWY
a3) Two-dose ChAdOx1 nCoV-19 5x10  vp (Abs 260) prime and 0.5mL | N=30

N=10

N= up to 30 from 1a1 | Adults aged 56 – 69 years |

CONFIDENTIAL

|                              |                                                                                                                                                                                                                                                                                                                                                                                                                                                                                                      |                                                                                                         |                               |
|------------------------------|------------------------------------------------------------------------------------------------------------------------------------------------------------------------------------------------------------------------------------------------------------------------------------------------------------------------------------------------------------------------------------------------------------------------------------------------------------------------------------------------------|---------------------------------------------------------------------------------------------------------|-------------------------------|
|                              | 
(3.5 – 6.5 × 10^10 vp, Abs 260, corrected for PS80) boost*, OR
 
a4) Two-dose MenACWY,
 
b1) Two dose ChAdOx1 nCoV19 vaccine, 5x10^10vp (Abs 260) prime and 2.2x10^10vp (qPCR) boost* (4-6 weeks apart), OR
 
b2) Two-dose MenACWY (4-6 weeks apart)
                                                                                                                                                                                             | 
N= up to 10 from 1a2
 
N=30
 
N=10
                                                     |                               |
| Group 2****                  | 
a1) Single dose ChAdOx1 nCoV19 vaccine, 5x10^10vp (Abs 260)*, OR
 
a2) Single dose MenACWY (4-6 weeks apart)
 
a3) Two-dose ChAdOx1 nCoV-19 5x10^10vp (Abs 260) prime and 0.5mL (3.5 – 6.5 × 10^10 vp, Abs 260, corrected for PS80) boost*, OR
 
a4) Two-dose MenACWY
 
b1) Two dose ChAdOx1 nCoV19 vaccine, 5x10^10vp (Abs 260) prime and 2.2x10^10vp (qPCR) boost * (4-6 weeks apart), OR
 
b2) Two-dose MenACWY
 | 
N=50
 
N=10
 
N= up to 50 from 2a1
 
N= up to 10 from 2a2
 
N=50
 
N=10
 | Adults aged 70 years or older |
| Group 4**
(n= up to 3550) | 
a1) Single dose ChAdOx1 nCoV19 vaccine, 5x10^10vp (Abs 260)*OR
 
a2) MenACWY
 
b1) Two dose ChAdOx1 nCoV19 vaccine, 5x10^10vp (Abs260) prime and 2.2x10^10vp (qPCR) boost* (4-6 weeks apart) OR
                                                                                                                                                                                                                                                       | 
N=up to 1775
 
N=up to 1775
 
N= up to 50 (from 4a1)
                                   | Adults aged 18 – 55 years     |

CONFIDENTIAL

|             |                                                                                                                                                                                                                                                                                                                                                                                                                                                                                                                                                                                                                                                                                                                         |                                                                                                                                                                                   |                         |
|-------------|-------------------------------------------------------------------------------------------------------------------------------------------------------------------------------------------------------------------------------------------------------------------------------------------------------------------------------------------------------------------------------------------------------------------------------------------------------------------------------------------------------------------------------------------------------------------------------------------------------------------------------------------------------------------------------------------------------------------------|-----------------------------------------------------------------------------------------------------------------------------------------------------------------------------------|-------------------------|
|             | 
b2) Two dose MenACWY
 
c1) Two dose ChAdOx1 nCoV19 vaccine, <math>5 \times 10^{10}</math>vp (Abs260) prime and 0.5mL (<math>3.5 - 6.5 \times 10^{10}</math> vp, Abs 260, corrected for PS80) boost* OR <math>5 \times 10^{10}</math>vp (qPCR) boost (at least 4 weeks apart) OR
 
c2) Two dose MenACWY
                                                                                                                                                                                                                                                                                                                                                                                                 | 
N= up to 50 (from 4a2)
 
N= up to 1725 (from 4a1)
 
N= up to 1725 (from 4a2)
                                                                                     |                         |
| Group 5**** | 
a1) Single dose ChAdOx1 nCoV19 vaccine, <math>5 \times 10^{10}</math>vp, (Abs 260)* OR
 
a2) MenACWY
 
a3) Two-dose ChAdOx1 nCoV-19 <math>5 \times 10^{10}</math>vp (Abs 260) prime and 0.5mL (<math>3.5 - 6.5 \times 10^{10}</math> vp, Abs 260, corrected for PS80) boost*
 
a4) Two-dose MenACWY
 
b1) Single dose ChAdOx1 nCoV19 vaccine, <math>5 \times 10^{10}</math>vp, (qPCR)* OR
 
b2) Men ACWY MenACWY (B-cell immunology only)
 
c1) Single dose ChAdOx1 nCoV19 vaccine, <math>5 \times 10^{10}</math>vp, (qPCR)* OR
 
c2) MenACWY (B and T-cell immunology)
 
d1) Two-dose ChAdOx1 nCoV19 vaccine, 0.5mL (<math>3.5 - 6.5 \times 10^{10}</math> vp, Abs 260,
 | 
N= 50
 
N=50
 
N = up to 50 from 5a1
 
N = up to 50 from 5a2
 
N= up to 25
 
N= up to 25
 
N= up to 25
 
N= up to 25
 
N= up to 50
 | Adults aged 18-55 years |

CONFIDENTIAL

|                                       |                                                                                                                                                                                                                                                                                                                                                                                                  |                                                                                                               |                                  |
|---------------------------------------|--------------------------------------------------------------------------------------------------------------------------------------------------------------------------------------------------------------------------------------------------------------------------------------------------------------------------------------------------------------------------------------------------|---------------------------------------------------------------------------------------------------------------|----------------------------------|
|                                       | 
corrected for PS80)*, (4-6 weeks apart)
OR
d2) Men ACWY
 
e) Two-dose ChAdOx1 nCoV-19 vaccine (Covishield <math>0.9 \times 10^{11}</math> vp/mL), 0.5mL (4-6 weeks apart)
 
f) Two-dose ChAdOx1 nCoV-19 vaccine (Covishield <math>0.9 \times 10^{11}</math> vp/mL), 0.25mL prime and 0.5mL boost (4-6 weeks apart)
                                                      | 
N= up to 10
 
N= up to 15
 
N= up to 15
                                                      |                                  |
| 
Group 6***
(n= up to 6000)
 | 
a1) ChAdOx1 nCoV19 vaccine, <math>5 \times 10^{10}</math>vp (qPCR)* OR
 
a2) MenACWY
 
b1) Two dose ChAdOx1 nCoV-19 vaccine, <math>5 \times 10^{10}</math>vp (qPCR) prime and 0.5mL (<math>3.5 - 6.5 \times 10^{10}</math> vp, Abs 260, corrected for PS80) boost* OR <math>5 \times 10^{10}</math>vp (qPCR) boost* (at least 4 weeks apart)
OR
 
b2) Two dose MenACWY
 | 
N = up to 3000
 
N = up to 3000
 
N = up to 3000 (from 6a1)
 
N = up to 3000 (from 6a2)
 | 
Adults aged 18 – 55 years
 |
| 
Group 7
                        | 
a1) Single dose ChAdOx1nCoV19 vaccine, <math>5 \times 10^{10}</math>vp (qPCR)*, OR
 
a2) Single dose MenACWY
 
b1) Two dose ChAdOx1nCoV19 vaccine, <math>5 \times 10^{10}</math>vp (qPCR)* (4-6 weeks apart),
OR
 
b2) Two-dose MenACWY (4-6 weeks apart)
                                                                                                              | 
N=30
 
N=10
 
N=30
 
N=10
                                                               | 
Adults aged 56 – 69 years
 |

CONFIDENTIAL

|          |                                                                                                                                                                                                                                                                                                                                                                                                                               |                                                 |                                                                       |
|----------|-------------------------------------------------------------------------------------------------------------------------------------------------------------------------------------------------------------------------------------------------------------------------------------------------------------------------------------------------------------------------------------------------------------------------------|-------------------------------------------------|-----------------------------------------------------------------------|
| Group 8  | 
a1) Single dose ChAdOx1nCoV19 vaccine, <math>5 \times 10^{10}</math>vp (qPCR)*, OR
 
a2) Single dose MenACWY
 
b1) Two dose ChAdOx1nCoV19 vaccine, <math>5 \times 10^{10}</math>vp (qPCR) prime and 0.5mL (<math>3.5 - 6.5 \times 10^{10}</math> vp, Abs 260, corrected for PS80) boost* OR <math>5 \times 10^{10}</math>vp (qPCR) boost (4-6 weeks apart), OR
 
b2) Two-dose MenACWY (4-6 weeks apart)
 | 
N=50
 
N=10
 
N=50
 
N=10
 | Adults aged 70 years or older                                         |
| Group 9  | 
a1) Two dose ChAdOx1 nCoV19 vaccine, 0.5mL (<math>3.5 - 6.5 \times 10^{10}</math> vp, Abs 260, corrected for PS80)* (4-6 weeks apart) OR
 
a2) Two dose MenACWY
                                                                                                                                                                                                                                                   | 
N= approx. 500
 
N= approx. 500
     | Adults aged 56 – 69 years                                             |
| Group 10 | 
a1) Two dose ChAdOx1 nCoV19 vaccine, 0.5mL (<math>3.5 - 6.5 \times 10^{10}</math> vp, Abs 260, corrected for PS80)* (4-6 weeks apart) OR
 
a2) Two dose MenACWY
                                                                                                                                                                                                                                                   | 
N= approx. 500
 
N= approx. 500
     | Adults aged 70 years or older                                         |
| Group 11 | Two dose ChAdOx1 nCoV19 vaccine, 0.5mL ( $3.5 - 6.5 \times 10^{10}$ vp, Abs 260, corrected for PS80)* (4-6 weeks apart)                                                                                                                                                                                                                                                                                                       | N=up to 60                                      | Adults aged 18-55 who previously received a ChAdOx1 vectored vaccine. |
| Group 12 | Two dose ChAdOx1 nCoV19 vaccine, 0.5mL ( $3.5 - 6.5 \times 10^{10}$ vp, Abs 260, corrected for PS80)* (4-6 weeks apart)                                                                                                                                                                                                                                                                                                       | N=up to 60                                      | HIV positive adults aged 18-55                                        |

\* See section 8.5 for further information on dosing

\*\* A subset of up to 100 participants in group 4a will be invited to receive a booster dose in 4b, keeping the overall sample size in group 4 the same. All remaining participants in group 4a will be invited to receive a booster dose in 4c, keeping the overall sample size in group 4 the same.

\*\*\* Participants in group 6a will be invited to receive a booster dose in 6b, keeping the overall sample size in group 6 the same

\*\*\*\* Participants in groups 1a (a1 and a2), 2a (a1 and a2) and 5a (a1 and a2) will be invited to receive a booster dose in the respective a3 and a4 groups, keeping the overall sample size in group 1a, 2a and 5a the same.

